In summary, no studies exist investigating the effectiveness of positive psychology interventions for BD patients. Furthermore, studies examining the effect of interventions aimed to enhance personal recovery or well-being for patients with BD are scarce and mostly used underpowered and weak methodological designs. For this reason, we aim to develop, implement and thoroughly investigate the effects of a multicomponent positive psychology intervention for the improvement of well-being and personal recovery for people with BD in an adequately powered randomized controlled trial. This will be the first study specifically evaluating a positive psychology intervention for patients with BD and will use a more sophisticated methodological design than studies before.

The primary objective is to evaluate the effectiveness of an eight-week multicomponent intervention *“*Living well with bipolar disorder*”* added to usual care (CAU) in BD patients in the euthymic phase. Primary outcome is the short and long term improvement of well-being and personal recovery. Secondly, the study aims to investigate whether the intervention in addition to CAU is more effective in improving social participation, and in improving depressive, manic, and anxiety symptoms. Thirdly, we will explore possible working mechanisms for intervention effects, including positive emotions, self-compassion, positive relationships and dampening of positive affect. Fourthly, the study aims to assess whether the intervention combined with CAU is more effective than CAU in reducing recurrence of depressive and (hypo)manic episodes in patients with BD in the long term. Finally, we aim to evaluate the cost-effectiveness of the intervention in addition to CAU for the treatment of euthymic patients with BD compared to CAU.

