## Method

### Study design

A pragmatic, parallel-group randomized non-blinded multicenter trial is used to investigate the effectiveness of a multicomponent positive psychology intervention to improve well-being and personal recovery in patients with BD. Since the outcome in BD I and BD II disorder may be different, the sample will be stratified accordingly. Patients in the experimental condition receive “Living well with bipolar disorder” in addition to CAU. Participants in the control condition receive CAU only. Both participants in the control and experimental condition receive CAU according to the Dutch multidisciplinary guideline for BD [13], consisting mainly of self-monitoring of mood and supportive group sessions focusing on functional problems, and psychopharmacotherapy. The study duration is 12 months for each individual and includes five measurement points. Immediately prior to the start of the intervention a baseline measurement is completed (T0), 4 weeks after the start of the intervention a mid-treatment measurement takes place (T1) and immediately following the intervention a post measurement will be conducted (T2). In addition, two follow-up measures will be conducted, 6 months (T3) and 12 months after baseline (T4). Figure 1 shows the intended flow of participants (Additional file 1).

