### Study measures

Almost all data being gathered during the trial are self-reported data that will be collected via an online survey program (https://www.qualtrics.com). In addition, one semi-structured telephone interview will be conducted 12 months after baseline to assess relapse. Participants will be asked to report demographical data including gender, age, marital and employment status, ethnicity and education, as well as the information about the past course of BD, at baseline. The primary outcome is well-being and secondary outcomes include personal recovery, social role participation and symptoms of depression, mania and anxiety. Additionally, processes of positive emotions, self-compassion and positive relationships are assessed and economic outcomes are used to calculate the cost-effectivness. An overview of the study measures at the different time points can be found in Table 2*.*

**Table 2 Tab2:** Overview of study parameters and measurement points

Questionnaire	Outcome	Screening	T0	T1	T2	T3	T4
			Pre-test	Mid-treatment^a^	Post-test	Follow-up^b^	Follow-up^c^
CGI-BP^d^	Global illness severity	X					
MINI	Diagnosis BD	X					
MHC-SF	Well-being	X	X	X	X	X	X
QPR	Personal recovery		X		X	X	X
s-SRPQ	Social participation		X		X	X	X
QIDS-SR	Depressive symptoms		X		X	X	X
ASRM	Manic symptoms		X		X	X	X
HADS-A	Anxiety symptoms		X		X	X	X
PANAS	Positive emotions		X	X	X		
SCS-SF	Self-compassion		X	X	X		
SPWB	Positive relationships		X	X	X		
RPA	Dampening of positive affect		X	X	X		
Telephone interviews	Relapse						X
EQ-5D-5 L	Quality of Life		X				X
TiC-P	Costs associated with psychiatric illness		X				X
Socio- demographics	Gender, age, education, marital status, living situation, ethnicity		X				

^a^4 weeks after intervention begin

^b^6 months after baseline

^c^12 months after baseline

^d^clinician reported

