#### Costs associated with psychiatric illness

The Trimbos and iMTA questionnaire on costs associated with psychiatric illness (TiC-P) [82] is a measure of health care utilization and production loss in patients with psychiatric disorders. Items are generic and not related to a specific psychiatric disease. A first part of the TiC-P includes 9 structured no/yes items on medical consumption (e.g. contact with specific mental health care providers). A second part (13 items) consists of the Short Form-Health and Labour Questionnaire, a generic instrument to collect data on productivity losses due to health problems (e.g. absence from work).

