#### Statistical analyses

Analyses will be done on both intention to treat (ITT) and per-protocol basis. The primary ITT analyses will be performed using linear mixed modelling (LMM) that adequately deals with missing at random data and the nested structure of repeated-measures data. LMMs with time, treatment and time-by-treatment interactions will be performed to test the effectiveness of the intervention in improving continuous primary and secondary outcomes of well-being, personal recovery, psychopathology, sef-compassion, positive relationships and dampening. Post-hoc independent t-tests with Holm-Bonferroni correction will be performed to test for significant between-group differences at all time-points. Based on estimated marginal means and corresponding standard errors from the LMM models, between-group standardized effect sizes will additionally be expressed as Cohen’s d with 95% confidence intervals (CI). Binary relapse data from the interviews will be analyzed with Kaplan Meyer survival estimates to compare the time to relapse and relapse rates between the intervention and control group. Differences in the proportion of relapsed patients and predictors of relapse will be additionally examined using generalized (binary) LMMs with post-hoc chi-square tests and relative risks (RR) with 95% CI to examine the significance and magnitude of differences at each follow-up point. Moderation and mediation analyses will be conducted to explore possible working mechanisms of the interventions. To calculate the cost-effectiveness of the intervention, quality adjusted life years (QALYs) will be taken into account as primary utility measure. QALYs will be calculated from the EQ-5D-5 L. The incremental cost-utility ratio (ICUR) will be calculated by dividing the difference in costs calculated from the TiC-P by the difference in the QALYs produced by the two groups. The ICUR is expressed as costs per QALY gained.

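### Utility is measured only at baseline and 12 months, and the cost difference is defined from the TiC-P, so the cost-utility ratio cannot see the year between and, as written, need not include the programme's own cost

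*Protocol article*

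**What the plan says.** The Background section of the Protocol article lists an economic evaluation as the last of its aims: "Finally, we aim to evaluate the cost-effectiveness of the intervention in addition to CAU". Study design sets the time frame: "The study duration is 12 months for each individual and includes five measurement points". These are T0 (baseline), T1 (mid-treatment, week 4), T2 (after the eight-week course), T3 (6 months) and T4 (12 months).

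Table 2 ("Overview of study parameters and measurement points") marks the two economic instruments twice each: "EQ-5D-5 L Quality of Life X X" and "TiC-P Costs associated with psychiatric illness X X". In both rows the marks stand under T0 and T4. T1, T2 and T3 are empty, although participants complete an online battery at each of them.

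Statistical analyses states "QALYs will be calculated from the EQ-5D-5 L" and defines the ICUR as the result obtained "by dividing the difference in costs calculated from the TiC-P by the difference in the QALYs produced by the two groups". The TiC-P, under Costs associated with psychiatric illness, "is a measure of health care utilization and production loss in patients with psychiatric disorders". No recall period is given for it, and no other source of costs is named.

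**The concern.** A QALY total over a year is the area under the utility curve. The programme runs in roughly the first two months, so its immediate effect falls between the only two utility measurements. So may relapses, which the trial aims to reduce and which the telephone interview dates by month. An analysis plan cannot recover utilities that were never collected.

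On costs, the resource under evaluation is the programme itself: therapist-led sessions, a trained therapist, a manual and a book. A patient questionnaire on care use and lost production does not record training or materials. Given at month 12, it records the sessions only if it looks back far enough. At stake is a published cost per QALY with a denominator that can be too small, zero or too large, and a numerator that may omit the cost of the programme being assessed.

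**Working it through.** The article gives no figure for utilities, QALYs, costs or the ICUR, so there is nothing of its own to reproduce. The check takes the schedule and works out what it can detect.

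**Inputs**
- Utility at months 0 and 12 only (Table 2).
- Possible further points: T2 at about month 2 and T3 at month 6 (Study design).
- Eight sessions of 2 h, groups of 8–10, one book per intervention participant (Intervention adjustments for euthymic BD patients).
- One-day workshop and treatment manual (Therapists training and treatment manual).
- Assumption: a between-group utility gain of 0.05 and no difference at baseline. The ratio of the two estimates does not depend on the value 0.05.

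**QALY difference**

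Trapezoid rule: sum of (average of adjacent differences × months between them) / 12. With points at 0 and 12 only, this reduces to half the difference at month 12, whatever happened before.

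| Course of the gain | T0, T2, T3, T4 | T0, T4 only |
|---|---|---|
| 0.05 by month 2, held to 6, zero at 12 | (0.05 + 0.20 + 0.15)/12 = 0.033 | 0 |
| 0.05 by month 2, held to 12 | (0.05 + 0.20 + 0.30)/12 = 0.046 | 0.05/2 = 0.025 |
| None to month 6, rising to 0.05 at 12 | (0.05 × 6/2)/12 = 0.0125 | 0.025 |

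The first gain is lost completely and the ICUR is undefined. The second is 45% too low (0.025/0.0458 = 0.55). The third is overstated twofold. The error can therefore go either way.

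**Programme cost**
- Sessions: 8 × 2 h = 16 therapist hours per group, or 16/10 = 1.6 to 16/8 = 2.0 h per participant. Training, manual and book come on top.
- End of the course: 56 days / 365.25 × 12 = 1.84 months. A questionnaire at month 12 must look back more than 12 − 1.84 = 10.2 months to reach even the last session. An 11-month recall reaches (1.84 − 1)/1.84 = 46% of the course, and a 12-month recall reaches all of it.
- Training, manual and book are not patient care use or production loss, so no recall period brings them in.

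**Other care costs**

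The share of the year covered by one TiC-P at T4 is recall/12. Under assumed recalls this is 25% at 3 months, 50% at 6 months and 100% at 12 months.

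**The case against.** The fairest reply is that a journal article condenses the protocol. Costing the programme, unit prices, the recall period and interval estimation usually belong in an analysis or economic plan, and their absence here is no error. The article says costs are calculated from the TiC-P; it does not say from nothing else. Programme inputs are fixed by the design and can be costed later without new participant data. The TiC-P asks about contacts with mental health care providers, so the sessions could be counted if recall is long enough.

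Much of this stands for costs. That part is therefore a matter of wording that should be settled, not a demonstrated omission. It does not stand for utilities, because the schedule is fixed in Table 2 and later analysis cannot fill in months that were not observed.

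Three stronger readings are tempting, and the article supports none of them:
- That costs miss most of the year. This holds for a recall under 6 months and fails for 12 months, and no recall is stated.
- That incremental cost is biased in favour of the intervention overall. Leaving out programme cost pushes that way, but unobserved care costs could push either way. For example, missing months in which the intervention reduced care use would count against it.
- That the cost-effectiveness aim cannot be answered. A two-point estimate is coarse, not impossible, and any ICUR is unstable when the QALY difference is near zero.

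Burden is also a fair point. The batteries are put at about 35 minutes, the TiC-P has 9 + 13 = 22 items, and the Discussion names attrition as a limitation.

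**Conclusion.** The concern holds for utilities without condition: nothing is observed between month 0 and month 12, and the two-point QALY difference is simply half the month-12 difference. In the illustrations it recovers between none and about 55% of an early gain and doubles a late one. The absolute values rest on the assumed gain of 0.05 and on the assumed shapes over time; the proportions rest on the shapes only.

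For costs it holds conditionally. As written, the numerator does not capture training, manual and book, and it captures the sessions only with a T4 recall beyond about 10 months. If programme cost is left out, that component lowers the incremental cost in the intervention's favour. The share of other care costs missed, and the net direction of any cost bias, are not established.

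This is a secondary aim. The primary outcome, its analysis and the sample size are untouched. The change is worth making because it is cheap and the missing utilities cannot be recovered afterwards.

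**What to change.** 1. Add the five-item EQ-5D-5L to the existing T2 and T3 online batteries, and compute QALYs as the area under the curve over T0, T2, T3 and T4.
2. State that the programme's cost (therapist hours, training, manual and book) is added to the TiC-P costs in the intervention arm, taken from a simple log per group. Make sure that sessions also reported on the TiC-P are not counted twice.
3. State the TiC-P recall period. At T4 it should cover the follow-up year; if it is shorter, give the TiC-P at T3 as well. A six-month recall at both T3 and T4 would cover the 12 months.

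The cost is a few more minutes of questionnaire at T2 and T3, more at T3 if the 22-item TiC-P is added, and a short cost record per group. No additional contact with participants is needed.

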### Statistical methods

#### Power calculation

The sample size calculation for this trial is conservatively based on the ability to detect at least a moderate effect of Cohen’s *d* = 0.60 in the post-hoc tests on the primary outcome (well-being) at post-intervention (T1). For a two-sided independent t-test with 80% power and *α* = 0.05, this requires 45 patients for both treatment groups. Taking a maximum drop-out rate of 20% into account, a total of 112 patients will need to be included for the per-protocol analysis.

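### The ICUR denominator has no stated baseline adjustment; read literally, chance imbalance in T0 utility enters the QALY difference and makes it needlessly imprecise

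*Protocol article*

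**What the plan says.** Under Statistical analyses, the article says "QALYs will be calculated from the EQ-5D-5 L". It forms the ICUR by "dividing the difference in costs calculated from the TiC-P" "by the difference in the QALYs produced by the two groups", and reports the result as a cost for each QALY gained. It does not say how utilities become a QALY, or whether the group difference is adjusted.

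Table 2 (Study measures) gives the schedule. The row reads "EQ-5D-5 L Quality of Life X X", and the two marks fall under T0 and T4. The TiC-P has the same two time points. Study design fixes the horizon: "The study duration is 12 months for each individual and includes five measurement points". Study procedure puts allocation after the baseline battery, so the T0 utility is a true pre-randomisation value.

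The same Statistical analyses section prescribes linear mixed models with time, treatment and their interaction for a named list of continuous outcomes. QALYs and costs are not on that list; they have only the ratio rule.

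**The concern.** The ratio is meant to describe QALYs gained because of the intervention. With utilities only at 0 and 12 months, the usual area under the curve gives the first measurement the same weight as the last, although the intervention cannot have affected it. If the arms differ at T0 by chance, half of that difference passes directly into the QALY difference, and more follows because T4 utility is correlated with T0 utility. The stratification factors that the article mentions are centre and bipolar type, so the design does not balance utility directly.

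Cost-effectiveness is a stated objective and the ICUR is its only stated summary. Its denominator is likely to be small, so avoidable noise there can change its size or its sign. The T0 utility that would remove much of this noise is already being collected.

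**Working it through.** **Inputs from the article.** EQ-5D-5L at T0 and T4; a 12-month horizon; 45 completers per arm (Power calculation).

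**The plan's own figure.** The article plans for "at least a moderate effect of Cohen’s *d* = 0.60" and continues "For a two-sided independent t-test with 80% power and *α* = 0.05". An exact t-test calculation gives 44.6, hence 45 per arm (power 80.4%), which agrees. Allowing for 20% dropout, 90/0.8 = 112.5, against the stated 112. The article gives no figure for utility SD, QALYs or the ICUR.

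**Assumptions, not in the article.** Two-point trapezoid; utility SD s = 0.20 (range 0.15–0.25) at both times; T0–T4 correlation r = 0.6 (range 0.4–0.8); true T4 utility gain 0.05.

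**Step 1, the QALY.** Over one year, QALY = (u0 + u12)/2. A T4 gain of 0.05 is therefore worth 0.05/2 = 0.025 QALY.

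**Step 2, standard errors of the group difference (n per arm).**
- Unadjusted: s × sqrt((1 + r)/2) × sqrt(2/n) = 0.20 × 0.894 × 0.2108 = 0.0377.
- Adjusted for u0: 0.5 × s × sqrt(1 − r²) × sqrt(2/n) = 0.5 × 0.20 × 0.80 × 0.2108 = 0.0169.

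**Step 3, their ratio.** s and n cancel, leaving sqrt(2/(1 − r)):

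| r | SE ratio |
|---|---|
| 0.4 | 1.8 |
| 0.6 | 2.2 |
| 0.8 | 3.2 |

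**Step 4, chance that the QALY difference has the wrong sign**, Φ(−effect/SE):
- Unadjusted: Φ(−0.025/0.0377) = Φ(−0.66) ≈ 25%.
- Adjusted: Φ(−0.025/0.0169) = Φ(−1.48) ≈ 7%.

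**Step 5, sensitivity.**
- Over the assumed SD and correlation ranges, still for a T4 gain of 0.05: 17–31% unadjusted, about 0.4–15% adjusted.
- With 56 per arm (112/2, no dropout) and the central assumptions: SEs 0.0338 and 0.0151, giving about 23% and 5%.
- With a smaller T4 gain of 0.03 (0.015 QALY), 45 per arm and the central assumptions: Φ(−0.40) ≈ 34% and Φ(−0.89) ≈ 19%.

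**Step 6, given an observed imbalance.** A baseline difference D shifts the expected unadjusted QALY difference by D(1 + r)/2. The SE of a chance baseline difference is 0.20 × 0.2108 = 0.042, so a deficit of 0.05 in the intervention arm is about 1.2 SE. At r = 0.6 it shifts the estimate by −0.05 × 0.8 = −0.040 QALY, more than the assumed true gain of 0.025.

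**The case against.** The strongest reply is that the article is silent rather than wrong. Its sentence is the generic definition of an ICUR, which a regression-adjusted difference would satisfy equally well. A condensed article may leave covariates to an analysis plan that is not shown. This stands to the extent that one cannot say the plan prescribes an unadjusted difference. However, the article does state a rule for the ratio, that rule has no baseline term, and QALYs are outside the models named for the other outcomes. The literal reading is the unadjusted one.

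The trapezoid is also not stated. If T4 utility alone were used, the central case gives SEs of 0.20 × 0.2108 = 0.0422 unadjusted and 0.20 × 0.80 × 0.2108 = 0.0337 adjusted, for an effect of 0.05. The wrong-sign chance would be about 12% against 7%, so the gain from adjustment is smaller but still present. A rule based on change from baseline would remove the direct half weight, but the article states none.

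A reader might infer that the unadjusted ratio is biased, or that adjustment would guarantee the right sign. Neither holds. Randomisation makes the unadjusted QALY difference unbiased over repeated trials; the harm is imprecision, and bias conditional on the imbalance observed. An adjusted estimate can still have the wrong sign. Nor is the ambiguity of a negative ICUR (better and cheaper, or worse and dearer) produced by this choice: it belongs to any such ratio.

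Finally, cost-effectiveness is the last of the listed objectives and the trial is sized on well-being. No conclusion on well-being or any clinical outcome is affected.

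**Conclusion.** The point holds as an avoidable loss of precision, not as an error in what the plan estimates. Read literally, the ICUR denominator admits chance T0 imbalance and has a standard error about 1.8 to 3.2 times what the same data could give, for correlations of 0.4 to 0.8. That ratio depends on the two-point area under the curve and on the correlation, not on the SD or the sample size. The wrong-sign figures, about 25% against 7%, rest additionally on an assumed SD of 0.20, a true T4 gain of 0.05 and 45 per arm; other values move both figures, as the sensitivity results show. The documents do not support saying that the plan specifies a raw difference. If a fuller plan already adjusts for T0 utility, one clarifying sentence settles the matter.

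**What to change.** In Statistical analyses, state how the QALY is calculated (for example, area under the line between T0 and T4 utilities). Then define the ICUR denominator as the treatment coefficient from a linear regression of the 12-month QALY on arm and T0 EQ-5D-5L utility.

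Two optional good-practice additions: adjust the cost difference for T0 TiC-P cost in the same way, and report incremental net monetary benefit with an interval beside the ICUR, which helps with the generic ambiguity of a negative ratio.

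The cost is one or two sentences and slightly more analysis. No further patients, visits or questionnaires are needed, because both instruments are already completed at T0.

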## Discussion

The presented study aims to examine the short- and long term effectiveness of the multicomponent positive psychology intervention *“*Living well with bipolar disorder*”* for euthymic BD patients to enhance personal recovery and well-being. In the present article, we described the intervention development process and several adaptations made to the original program to tailor the intervention for the target group. The study will be conducted in at least four different outpatient treatment centers in the Netherlands, all specialized in the treatment of BD. The intervention group will receive the intervention program in addition to CAU and the control group will receive CAU only.

Several potential limitations of the study have to be considered in advance. Firstly, since participants in this intervention are euthymic (i.e. not in a syndromal depressive, hypomanic or manic episode), results of the trial cannot be generalized to the entire patient group in all phases of BD. Secondly, the study will not be able to determine which specific elements of the interventions lead to possible effects of the intervention. Non-specific factors (e.g. social contact during group lessons or placebo effect) can thus not be ruled out as possible confounding variables. However, since we mainly aim to investigate the effect of the intervention in real-life clinical practice and our study concerns a pragmatic randomized trial, this limitation is not considered to impair the value of our study [84]. Further research could investigate the effectiveness of the intervention to determine whether the intervention is equally effective when taking non-specific factors into account. Thirdly, non-adherence to the intervention or dropout from the assessment might occur. Both types of attrition are likely to bias the results [85].

Our study will be the first to explore the effectiveness of a positive psychology intervention for the treatment of people with BD. In addition, it will be the first study to be implemented that focusses on the improvement of primarily personal recovery and well-being and uses a more sound design than existing pilot studies. The results of the study are expected to broaden the evidence base of clinical positive psychology and personal recovery and potentially generate novel treatment methods for people suffering from BD.

